### Chinese medicine diagnostic criteria of the spleen and stomach qi deficiency with damp-heat stasis syndrome

In acknowledgement of the consensus on diagnosis and treatment of chronic superficial gastritis with TCM (Shenzhen, 2009, Digestive Disease Branch of China Association for Traditional Chinese Medicine) [17], The People’s Republic of China TCM industry standards • the standards of diagnosis and efficacy of TCM syndromes [18], and the *Guidelines For Clinical Research On Chinese New Herbal Medicines (Trial Implementation)*[19], the CM diagnostic criteria of SSQDDSS in CNG patients are listed and include the following:

1. Primary symptom: epigastric pain.

2. Secondary symptoms: weakness and lassitude, dry mouth/bitter taste in mouth, loss of appetite, distention and fullness, loose stool or belching.

3. Tongue presentations: pale tongue, dark red tongue with ecchymosis or petechiae or enlarged and teeth-printed tongue.

4. Tongue coating: yellow or yellowish greasy coating.

5. Pulse presentations: thread and weak pulse or stringy pulse.

A diagnosis of SSQDDSS should include the primary symptom, the first two secondary symptoms and more than one of the remaining four secondary symptoms, simultaneously combined with tongue presentations and pulse presentations.

### Inclusion criteria

Inclusion criteria are:

1. Diagnosis of CNG according to Western medicine (moderate or severe level of chronic inflammation and/or active inflammation).

2. Diagnosis of spleen and stomach qi deficiency with damp-heat stasis syndrome, according to TCM syndrome differentiation.

3. Aged between 18 and 65 years.

4. Voluntary provision of written informed consent prior to enrollment.

### Exclusion criteria

Exclusion criteria are:

1. History of gastric surgery.

2. Combined gastric ulcer, duodenal ulcer, special types of gastritis or gastrointestinal hemorrhage.

3. Histopathological examination showing atrophic changes, intestinal metaplasia, dysplasia or suspected malignant changes in the gastric mucosa.

4. Serious comorbidities of heart, lung, liver, kidney or blood system (such as cardiac function above grade II, alanine aminotransferase (ALT) and/or aspartate aminotransferase (AST) greater than 1.5 times the upper limit of normal, creatinine (Cr) greater than the upper limit of normal and so on) or having a life-threatening illness (for example, tumor or AIDS).

5. Positive fecal occult blood test.

6. Having received TCM or Western medicines to treat CNG in the last 2 weeks.

7. Psychiatric disorders or a history of alcohol or drug abuse.

8. Female patients preparing for a baby, pregnant or lactating.

9. Allergic to the trial pills.

10. Currently participating or enrolled in another drug trial over the last three months.

11. Unclear TCM diagnosis of syndrome differentiation or too complicated SDs in TCM.

12. Having been judged inappropriate to participate in the trial by investigators.

### Rejection criteria

Rejection criteria include:

1. Misdiagnosis.

2. The trial drug is taken at doses <80% or >120% of the requirement, or is not taken as directed.

3. Patients do not cooperate or cannot complete follow-up.

### Withdrawal criteria

Withdrawal criteria include:

1. Intolerance to worsening conditions.

2. Quitting voluntarily.

3. Having manifestations of hemorrhage of the digestive tract, such as melena or hematemesis during the study.

4. Experiencing anaphylaxis following the trial drug’s administration.

5. Adverse medical events occurring during the study, such as severe liver function damage, malignant tumors in other system, and accidental pregnancy or other reasons, as judged by the investigators, that might make the patient unlikely to complete the study.

### Suspending early or terminating the entire study

The study may be suspended early or terminated in the event of the following:

1. Serious adverse event (SAE) caused by the trial drugs.

2. The effect of the test drug is poor or even completely ineffective.

3. Discovery of a blunder in the protocol or of a significant deviation between the protocol and actual practice

4. The decision to terminate the study being made by the pharmaceutical supervisory and administrative department or by the sponsors, for any reason.

### Concomitant treatments and forbidden drugs

Subjects will be permitted to continue concomitant treatment for comorbidities, such as hypertension, chronic bronchitis, stroke or skin disease, which will not affect the trial’s final results. However, they are forbidden to take any CM or Western medicine related to CNG, such as prokinetics, cholinergic agents, H2-receptor antagonists, proton pump inhibitors, mucosal-protective agents or antibiotics for the eradication of HP. Aspirin, nonsteroidal anti-inflammatory drugs, sedative hypnotics, antidepressants and opioids should be used sparingly. Each concomitant treatment should be documented strictly in the CRF, and once a subject is found to be taking forbidden drugs, he/she will be withdrawn from this study.

### Test drugs and blinding

The JWQTP and the dummy JWQTP will be manufactured by Anbang pharmaceutical Limited by Share Ltd, Hunan, China, with the approval of the CFDA for clinical studies only (Approval No. 2012 L02382). Of note, the dummy JWQTP is not exactly the same as the test pill in color and smell. To make a blind test possible, all of the drugs are concealed in unified, sealed and opaque packages with the same labels that contain the drug name, the approval number of the pill, functions, usage, dosage, storage conditions, expiration dates for use and the manufacturer’s name. The drugs are administered by an independent clinical assistant in each center, who takes responsibility for the drug’s distribution, storage and return. Any members who have access to the drug will not participate in case observations or efficacy evaluations. Each package contains one dose (six 1-g pills) with a variable ratio between the real drug and the dummy drug, according to the intervention protocol. Patients will be randomized to a high-dose group, low-dose group or placebo control group, in which they will take 6 g real drugs, 4 g real drugs + 2 g dummy drugs or 6 g dummy drugs, respectively. All drugs will be taken orally with water before each meal three times a day for 8 weeks. A follow-up visit will be scheduled every 2 weeks after treatment. Patients who have not made a full recovery from CNG after the clinical study will receive conventional treatment. Details of the procedures and content are shown in Figure 2.

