## Methods/Design

This current study is a phase II, multicenter, parallel-group, double-blind, randomized and placebo-controlled trial. The study will be conducted in compliance with the Declaration of Helsinki, Good Clinical Practice (GCP) Guidelines [13] and the requirements of clinical trials by the Drug Administration Law of the People's Republic of China, and will strictly observe all laws governing new TCM drugs. The study was approved by the CFDA (Approval No. 2012 L02382), and the protocol and informed consent were reviewed and approved by the West China Hospital of Sichuan University Clinical Trials and Biomedical Ethics Committee (No. TCM-2013-06). In addition, it was registered in the Chinese Clinical Trial Registry (ChiCTR-TRC-14004088). We will recruit subjects by advertising on the hospital’s notice board or through recommendations in the outpatient clinic. All patients must provide written informed consent. The trial is financially supported by Anbang Pharmaceutical Limited by Share Ltd, Hunan, China, which did not contribute to the study design, data collection, data management, analysis, interpretation of data or decision to submit the report for publication, except for the provision of all test drugs. Each trial center has a project manager who is responsible for the quality of research. Standard training will be required for all investigators before the trial. An independent trial inspector will pay regular visits to each center, check the case report forms (CRFs) and supervise the research to make sure it complies with the protocol throughout the trial. Figure 1 shows the flow chart of this trial.

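### The dummy pill differs from the active pill in color and smell and only the packaging masks it, so patient blinding is not assured for the self-reported outcomes

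*Protocol article*

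**What the plan says.** The Methods/Design section describes the study as a "phase II, multicenter, parallel-group, double-blind, randomized and placebo-controlled trial", and the abstract makes the same claim. The section Test drugs and blinding then adds a caveat: "Of note, the dummy JWQTP is not exactly the same as the test pill in color and smell".

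The remedy offered there is at package level: "all of the drugs are concealed in unified, sealed and opaque packages with the same labels". An independent assistant at each center handles the drug, and nobody with access to it takes part in observation or efficacy evaluation.

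The same section fixes what the patient finds on opening a pack. "Each package contains one dose (six 1-g pills) with a variable ratio between the real drug and the dummy drug", and by arm "they will take 6 g real drugs, 4 g real drugs + 2 g dummy drugs or 6 g dummy drugs, respectively". Dosing is frequent: "All drugs will be taken orally with water before each meal three times a day for 8 weeks".

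The primary outcome (Outcome measurement) is eradication of epigastric pain, judged from a 0 to 10 pain score taken at every visit. There are five secondary outcomes: endoscopy, histopathology, H. pylori eradication, TCM symptom scores and the 35-item PRO instrument. Under Data management, the statistician works with arms labelled A, B and C.

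**The concern.** An opaque pack conceals its contents only until it is opened, and the person who opens it is the patient. That same person supplies the pain score behind the primary outcome, the complaints behind the TCM symptom scores, and the PRO answers. Excluding drug handlers from evaluation and coding the arms for analysis protect staff and the statistician. Neither can remove a bias that is already in what the patient reports.

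The low-dose arm is the most exposed. Its packs hold two kinds of pill that the article itself says are not alike, so the patient can compare them at every dose. The visual cue also differs between the two active arms, which bears on the objective of describing a dose-effect relationship.

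At stake is how a positive result can be read. Reported pain can respond to expectation. If patients can tell or guess what they take, part of a difference on the VAS may reflect expectation, and this trial is meant to supply evidence for phase III.

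**Working it through.** **1. What each patient sees** (Test drugs and blinding; allocation from Randomization; total from Sample size calculation)

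- Patients per arm: 240 / 3 = 80.
- Packs opened per patient: 3 per day × 7 days × 8 weeks = 168.

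| Arm | Active pills per pack | Dummy pills per pack | Inside one pack |
|---|---|---|---|
| High dose | 6 | 0 | one kind |
| Low dose | 4 | 2 | two kinds, side by side |
| Placebo | 0 | 6 | one kind |

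One third of patients (80 / 240) have a direct comparison in the pack. The others have none. For them a difference could show only through the smell or color of the pill itself, or by comparison with another patient's pack.

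**2. Whom each safeguard covers**

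| Safeguard | Covers | Covers the patient after opening? |
|---|---|---|
| Opaque, sealed, identically labelled packs | everyone, until opening | no |
| Drug handlers kept out of evaluation | staff evaluators | no |
| Arms coded A, B, C for analysis | statistician | no |

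**3. Which outcomes are exposed**

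The primary outcome and two of the five secondary outcomes (TCM symptom scores, PRO) rest on what the patient reports. Endoscopy, histopathology and H. pylori eradication depend less on expectation.

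**4. The plan's own figure**

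The sample size section gives 66 per group for 55% against 30%, α = 0.05, power 0.85; the statistical section specifies two-sided tests. With the unpooled normal approximation:

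n = (1.960 + 1.036)² × (0.55 × 0.45 + 0.30 × 0.70) / 0.25² = 65.7, rounded up to 66.

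This reproduces the stated number. It neither supports nor weakens the present point. It supplies the 30% placebo rate used next.

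**5. Illustration of what a bias would do (assumed, not estimated)**

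The documents give no figure for expectation bias, so a range is shown. Assume that the drug has no effect, that the true rate is 30% in both arms, and that expectation adds b to the reported rate in one active arm. The 30% is the article's placebo rate for total efficiency, taken here as the pain-eradication rate. The chance of a significant result in favor of the drug is approximately

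Φ[(b − 1.96 × SE₀) / SE₁], with SE₀ = √(2p̄(1 − p̄)/n), SE₁ = √((p₁(1 − p₁) + p₀(1 − p₀))/n), p₀ = 0.30, p₁ = 0.30 + b and p̄ = (p₁ + p₀)/2.

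Example with n = 80, b = 0.10: p̄ = 0.35, 1.96 × SE₀ = 0.1478, SE₁ = 0.0750, so Φ[(0.10 − 0.1478)/0.0750] = Φ(−0.637) = 0.262.

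| Assumed gain b | n = 80, approximation | n = 80, exact two-sided chi-square | n = 66, approximation | n = 66, exact two-sided chi-square |
|---|---|---|---|---|
| 5 points | 9.9% | 10.5% | 8.9% | 9.6% |
| 10 points | 26.2% | 26.5% | 22.4% | 23.1% |
| 15 points | 50.0% | 49.8% | 42.8% | 43.6% |

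The exact columns count significance in either direction. With no bias, the approximation gives 2.5% in favor of the drug. All three assumed gains lie below the planned difference of 25 points.

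**The case against.** A reader might infer that the pills are visibly different and that the double-blind therefore fails. The documents do not support that. The article says only that the match in color and smell is not exact and gives no size; the difference could be slight. High-dose and placebo packs are each uniform, so those patients have nothing in the pack to compare with. A low-dose patient who notices two kinds of pill can deduce the arm only if he or she knows how the packs are made up, and what patients are told is not in the text at hand. This objection stands: the supportable conclusion is that blinding is not assured, not that it is broken.

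A reader might also take the percentages as the likely inflation of false positives. They are not. The gains are assumed, and nothing in the documents anchors them. Nor does seeing mixed pills by itself show that expectation is higher than on placebo. The figures show what follows if a bias occurs.

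Nor are most secondary outcomes self-reported: only two of five are.

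Finally, a condensed article may leave a treatment-guess question to the full protocol or case report form, so its absence is not held against the plan here. The authors also disclose the mismatch openly. What remains is narrower: the article states a difference between the pills, states its remedy, and that remedy does not reach the patient on whom the primary outcome depends.

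**Conclusion.** The concern holds in this limited form. The label double-blind is unqualified, while the measures described secure the blinding of staff evaluators and the analyst but not that of the patient. The outcomes affected are the VAS pain eradication rate, the TCM symptom scores and the PRO. Exposure is clearest in the low-dose arm: 80 of 240 patients, each opening about 168 mixed packs. In the other two arms unblinding is possible but not certain. How far results would be distorted cannot be determined from the documents. If expectation added 5, 10 or 15 points in one active arm, with a true 30% rate in both arms and 80 per arm, about 10%, 26% or 50% of trials would be significant. That range rests wholly on the assumed gains.

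**What to change.** The Trial status section says recruitment is still being prepared, so the preferred change remains open: mask the pills themselves by matching the dummy to the active pill in color and smell, if the batch can still be changed. What that would cost, or whether approval would be needed, cannot be judged from the documents.

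If the pills stay unmatched:

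1. Replace the unqualified double-blind claim with a statement that staff evaluators and the analyst are blinded but blinding of patients is not assured. Limit the conclusions on the VAS, TCM symptom scores and PRO accordingly. The label assessor-blind would not serve, because for the pain score the patient is in effect the assessor.
2. Unless the full protocol already has one, add a treatment-guess question early in treatment and again at visit six, and report a blinding index for each arm. Late guesses are confounded by perceived benefit, so the early one should carry more weight.
3. Endoscopy, histopathology and H. pylori eradication may be reported as less exposed to expectation, but not as confirmation of an effect on pain. The Discussion itself says dyspeptic symptoms have no clear relation to endoscopic grade or histology.

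The cost of these three steps is one question on the case report form, asked twice, a small additional analysis and a more modest claim.

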**Figure 2 F2:**
[figure not shown]
Study schedule for patients.

### Outcome measurement

#### Primary outcome

The eradication of epigastric pain is considered the primary outcome to evaluate therapeutic effects. The visual analogue scale (VAS) score (0 to 10 numeric pain intensity scale) for epigastric pain was measured at every visit, ranging from 0 to 10, where a score of 0 suggests no epigastric pain and a score of 10 indicates the most severe epigastric pain. The eradication of epigastric pain is defined as a score of VAS that stops rising after dropping to 0 during the study. The eradication rate of epigastric pain will be compared among the three groups, together with the change in VAS scores before and after treatment in each group.

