#### Secondary outcomes

##### Endoscopic and histopathological examination

The change in red plaques, hemorrhagic spots/plaques, erosion and bile reflux at endoscopy and the grade of active chronic inflammation and chronic inflammation in the gastric mucosa, depending on the histopathological examination of biopsy specimens, will be compared between visits one and six, according to the consensus on CG in China.

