#### The change in the patient-reported outcome instrument for chronic gastrointestinal diseases

Although the symptoms of chronic gastritis are not specific, the relief of clinical symptoms remains a major therapeutic aim. The patient-reported outcome (PRO) instrument for chronic gastrointestinal diseases (http://www.proqolid.org/) [20], a 6-dimension, 35-item instrument, will be performed on visits one and six, and the results will be used to compare the two visits to assess any changes in quality of life. The 35 items of the instrument are the following: fatigue, disturbed sleep, no hunger sensation, decreased appetite, afraid of society, dry mouth or bitter taste in mouth, bad breath, pharyngeal foreign body sensation, acid regurgitation, hiccup or belching, nausea or vomiting, burning pain behind the sternum, retrosternal pain, stomachache, gastric distension, gastric discomfort, stomach burning, abdominal pain, abdominal distension, degree of retrosternal pain, degree of heartburn, degree of stomachache, degree of gastric distension, degree of abdominal pain, degree of abdominal distension, diarrhea, constipation, incomplete sensation after defecation, defecation urgency, weight loss, emotional fluctuation, anxiety or nervous, worry about disease, impact on social activities and impact on family status and function. All of the items fall into five levels, which are scored as 0, 1, 2, 3 or 4, except for decreased appetite, which is grouped into four levels and scored as 0, 1, 2 or 3. The final score will be determined by the sum of all symptom scores.

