#### Sample size calculation

Based on the preliminary results of clinical research, no less than an estimated 55% total efficiency will be obtained with JWQTP treatment and approximately 30% will be obtained with the intervention of a placebo. Using a superiority test, no fewer than 66 subjects should be enrolled based on α = 0.05, β = 0.15 and power = 0.85 in each treatment group. Allowing for a 20% drop-out, we therefore propose the recruitment of a total sample size of 240 patients, with average distributions among the three groups.

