An analysis of variance (ANOVA) or chi-square test will be used to compare baselines among patients, including demographic data, vital signs, history of diseases, basic treatment and so on. For the comparison of variations from the baseline to endpoint, Student’s t-test will be performed on variables with normal distributions, and the Wilcoxon rank sum test will be performed on variables with non-normal distributions. The evaluation of therapeutic effects will primarily be performed between baseline and visit six, in compliance with PPS, or the time to withdraw from the study, in compliance with FAS. In addition, the changes from baseline to visits two, three, four or five will be evaluated. For continuous variables regarding therapeutic effect, an ANOVA will be used for multiple comparisons of variation from baseline among different groups, and Dunnett’s tests will be used for comparisons within a group. A covariance analysis, adjusted for the baseline covariate, will be used to evaluate the differences of the symptom scores, VAS scores and PRO instrument scores among the groups considering the center effect. The least square mean in each group and the 95% confidence intervals of mean differences among groups will be calculated. The Cochran-Mantel-Haenszel test, stratified by center effect, and the logistic regression model, adjusted for covariates, will be used on categorical variables in addition to the chi-square test, Wilcoxon rank sum test or Fisher’s exact test. The total drop-out rate in each group will be compared with the drop-out rate due to AEs for drop-out analyses using chi-square test or Fisher’s exact test. For safety analyses, we will perform the chi-square test or Fisher’s exact test to evaluate the incidence rate of AEs among the groups and describe AEs using descriptive statistics through listing.

All statistical tests will be performed by an independent statistician using SAS 9.2, assuming a two-sided test and a 0.05 level of significance.

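### Within-group before-after comparisons stand beside the planned between-group analyses and are not labelled descriptive; endoscopy, histology and PRO outcomes should name the contrast with placebo

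*Protocol article*

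**What the plan says.** All references are to the protocol article.

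- **Primary outcome.** The section opens: "The eradication of epigastric pain is considered the primary outcome to evaluate therapeutic effects". It then says "The eradication rate of epigastric pain will be compared among the three groups", and the same sentence continues "together with the change in VAS scores before and after treatment in each group". The Abstract gives the eradication rate alone as primary.
- **Endoscopic and histopathological examination.** The changes and grades "will be compared between visits one and six, according to the consensus on CG in China". No contrast between arms is named.
- **Patient-reported outcome instrument.** It is completed at visits one and six, and "the results will be used to compare the two visits to assess any changes in quality of life". Again no arm is named.
- **Statistical analysis.** Change from baseline is compared among groups by ANOVA. A baseline-adjusted covariance analysis "will be used to evaluate the differences of the symptom scores, VAS scores and PRO instrument scores among the groups considering the center effect", with 95% confidence intervals for the differences among groups. Categorical variables get a center-stratified Cochran-Mantel-Haenszel (CMH) test and logistic regression. The same section gives Dunnett's test to comparisons inside a group and sets a two-sided 0.05 level for all tests.
- **Sample size calculation.** The assumed response is at least 55% on JWQTP, while "approximately 30% will be obtained with the intervention of a placebo".
- **Inclusion criteria.** Entry requires a "moderate or severe level of chronic inflammation and/or active inflammation".

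**The concern.** A before-after test inside one arm asks whether scores moved over 8 weeks. It does not ask whether JWQTP moved them, because the placebo arm does not enter the calculation. Using a correct paired test does not cure this.

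The protocol itself expects movement without active drug. It assumes a placebo response of about 30%, and its Discussion describes symptoms that recur and respond to psychological, social and dietary influences. For histology, the grade that qualifies a patient for entry is also the baseline, so some fall by regression to the mean is expected without any treatment.

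The trial is meant to inform a phase III program and its dose. If two active arms each show a significant fall from baseline, and that result is reported next to the primary outcome, it is easily taken as support for efficacy. For endoscopy and histology the risk is greater: the outcome text gives only the visit contrast, the ANCOVA sentence does not list them, and the CMH sentence does not say which arms are contrasted.

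**Working it through.** **1. The plan's own figure.** Inputs from Sample size calculation: 55% against 30%, two-sided α = 0.05, power 0.85. The unpooled normal approximation gives n = (0.55×0.45 + 0.30×0.70) × (1.960 + 1.036)² / 0.25² = 0.4575 × 8.976 / 0.0625 = 65.7, so 66 per group, as stated. The trial is therefore sized on a between-arm contrast. The planned 240 patients give 240/3 = 80 per arm, or 80 × 0.80 = 64 after the 20% drop-out.

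**2. What a within-group VAS test would do with an inert pill.** The statistic is t = mean fall / (SD of change / √n). The article gives no baseline VAS, no SD of change and no mean placebo change, so these are assumed:
- baseline mean 3 or 5, SD 1.5, on a whole-number scale;
- a share of patients falls to VAS 0;
- the others have random change with mean zero and SD 1 to 2.5, cut off at 0 and 10.

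Two settings at n = 80 and 30% responders, worked by hand from the simulated mean and SD of change:
- Baseline 3, SD of random change 2.5: mean fall 0.78, SD 2.50, so t is centered at 0.78 / (2.50/√80) = 2.8. Simulated rate of a significant fall: 0.78.
- Baseline 5, SD of random change 1: mean fall 1.50, SD 2.59, so t is centered at 1.50 / (2.59/√80) = 5.2. Simulated rate: 1.00.

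Range over all settings (20,000 simulated trials each):

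| Share falling to VAS 0 | n per arm | Significant within-group fall |
|---|---|---|
| 30% | 80 | 0.78-1.00 |
| 30% | 64 | 0.68-1.00 |
| 20% | 80 | 0.38-0.99 |
| 10% | 80 | 0.07-0.69 |

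**3. The same question without the VAS 0 assumption.** Power of a paired t-test at n = 80, with SD of change 1.5 to 3: a mean fall of 0.5 points gives 0.31-0.84, and 1.0 point gives 0.84-1.00. With no mean change it is 0.05.

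**4. Between-arm tests on the same kind of data.** Three identical arms of 80, 30% falling to VAS 0, baseline mean 4.5, both SDs 1.5. The within-group test is significant in 99.8% of trials per arm, and in both active arms in 99.7%. ANOVA on VAS change among groups rejects in 5.1%, and the three-group chi-square on eradication in 5.1%.

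**5. Other outcomes.** The VAS figures cannot be carried over. For histology, a simulation of selection on grade alone gave 8-42% as the assumed repeat-biopsy correlation fell from 0.9 to 0.5. That result also depends heavily on the assumed distribution of grades, which the article does not give, so only the direction is usable. The endoscopic features and the PRO score have no entry threshold and no stated placebo change, so no figure can be given for them.

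**The case against.** The strongest reply is that the randomized comparison is already in place. The eradication rate is the declared primary outcome and is compared among groups. The VAS clause hangs on that same sentence, so it can be read as each group's change also being compared among groups. The analysis section supports this reading, with ANOVA and ANCOVA among groups for VAS and the ANCOVA also covering PRO. The outcome sections can be taken to say what is measured and when, leaving the contrast to the analysis section. The sentence on Student's t-test and the Wilcoxon rank sum test for change from baseline is not good evidence of within-group testing either, since the rank sum test compares independent samples. A ranking of supportive p-values is often left to an analysis plan, which is not shown.

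Most of this stands. A reader might infer that a within-group VAS change is itself the primary endpoint, or that an inert pill would appear effective almost every time on all these outcomes. The documents support neither. Eradication alone is declared primary, no passage lets a within-group p-value establish efficacy, and the high rates apply only to VAS under an assumed 30% fall to VAS 0.

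What does not fall away is the text itself. The Dunnett clause plans comparisons inside a group, although Dunnett's test compares several groups with one control. The endoscopy, histology and PRO outcomes name only the two visits. This is a contrast the article states badly, not a detail it omits.

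**Conclusion.** The point holds as a fault in stated contrasts that should be corrected, not as a fault in the primary comparison. The plan keeps within-group comparisons at two-sided 0.05 next to sound between-group analyses without saying that only the latter bear on efficacy. For endoscopy and histology it never states the arm contrast explicitly.

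For VAS the risk of a misleading significant result is large if the placebo response is near the protocol's 30%, and much smaller at 10%. It rests on assumed baseline values and SDs, and on reading a total efficiency rate as a fall to VAS 0. For histology only the direction of the bias is supported, and for endoscopy and PRO no size is claimed.

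**What to change.** - **Primary outcome:** replace the clause on change in each group with the difference in VAS change between each JWQTP dose and placebo, estimated by the ANCOVA already planned.
- **Endoscopic and histopathological examination:** state that the change from visit one to visit six is compared between each JWQTP dose and placebo, by the center-stratified CMH test for the graded findings.
- **Patient-reported outcome instrument:** state the same contrast, by the planned ANCOVA.
- **Statistical analysis:** use Dunnett's test for each dose against placebo instead of within a group. Label within-group changes descriptive, reported as mean change with 95% confidence interval and supporting no efficacy conclusion.

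The cost is wording only: no new data, visits or patients, and the Trial status section says recruitment was still being prepared. The downside is that within-group p-values can no longer be reported as efficacy results.
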